## Discussion

Given the high level of children’s dental caries in Saudi Arabia, the cultural norms of only visiting the dentist when in pain [2], and the availability of free dental services through the Ministry of Health, school-based screening could be an appropriate intervention for the epidemic of childhood dental caries in Saudi Arabia. While studies in other countries have examined the impact of school screening on dental visits and dental caries and showed variation in their results [9–15], this study goes one step further by referring the children to a specific healthcare facility with a system in place to handle referred children. Compared to studies in western countries that showed no effectiveness of dental screening [9–11, 13, 15], the population of Saudi Arabia could be different as asymptomatic dental visits are uncommon [2].

The findings of the proposed research will provide important information on the potential impact of school-based dental screening on untreated dental caries and the uptake of dental services. If the research shows a positive impact it will set the scene for recommending the implementation of school-based dental screening nationally. A positive finding will also provide the grounds for continuation of any existing screening programme in other parts of the country. The findings of this study will also highlight the importance of the ongoing monitoring of such programmes and continuous evaluation of their effectiveness. Contrarily, if the study does not show any benefit, it will highlight the importance of adequately examining the effectiveness and cost-effectiveness of any existing programmes.

Using two different outcome measures, reflecting uptake of services and clinical outcome, will help us disentangle where the screening programme might have failed. An increase in use of dental services without differences in clinical outcome would reflect issues with services but not with the screening tool. On the other hand, lack of effectiveness in both uptake of services and clinical outcome will reflect problems with the overall screening process.

The selected study design addresses some of the methodological limitations of previous studies [7, 8]. Data collection on participants’ socioeconomic and behavioural factors will help accounting for baseline differences between the two trial groups (if they are unbalanced after randomisation) that might impact use of dental services [21]. However, this study must be conducted with relatively limited resources as part of PhD project and will probably not answer all relevant questions on the effectiveness of school dental screening in Saudi Arabia. Future research should build upon what we are starting in this study, by looking into cost-effectiveness analysis and reasons behind any lack of effectiveness. A national study could also provide more information on effectiveness in different parts of the country.

Finally, it is worth noting that the education system in Saudi Arabia is segregated by children’s gender. Due to cultural restrictions, female dentists cannot access boys-only schools and vice versa. Although we have recruited and trained separate teams for accessing boys- and girls-only schools, access to both types of schools are heavily dependent on approval from the Ministry of Health as the principal investigator, who will oversee the entire fieldwork, is female. This might result in a male-to-female ratio different to 1-to-1.

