**Discussion:**

This project should provide high level of evidence on the clinical benefits of school dental screening. The findings should potentially inform policies related to the continuation/implementation of school-based dental screening in Saudi Arabia.

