All seven RCTs had a limited scope to dental screening, merely devoted to providing information to parents [7, 8]. No further attempts for follow-up communication and/or provision of assistance to parents with booking appointments was included [9–15]. A successful screening programme requires more than just the screening test; it should have a supporting system to ensure that those needing treatment are able to obtain it [6, 16, 17]. The provision of free dental services does not solve the problem as shown in the UK studies [9–11, 13, 15]. These extra efforts and costs to facilitate contact of screened-positive individuals with health services must be balanced against potential gains (clinical benefits) of the screening programme. Given the above reasons, it was not surprising that systematic reviews concluded that there is a need to conduct a well-designed trial with an intensive follow-up group [7, 8]. The present trial addresses these gaps in knowledge and methodological challenges.

The primary aim is to evaluate the effectiveness of two alternative approaches for school-based dental screening (referral to a specific treatment facility versus current practice —i.e. an information letter advising parents to take their child to a dentist—) in promoting dental attendance and reducing untreated caries among primary schoolchildren in Saudi Arabia. A secondary aim is to determine the effectiveness of school-based dental screening among population subgroups (two subgroups will be specifically considered, namely children who were screened positive and children who reported being regular attenders at baseline).

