### Trial interventions

Children in both groups will be examined for dental caries. The difference between the two trial groups lies in the referral mechanism. A comparison against no intervention was disregarded due to ethical concerns (children would be examined and not informed of their oral problems). Those having untreated dental caries according to the World Health Organisation (WHO) [20] criteria will be considered screened positive and referred according to their allocated group. All others will be considered screened-negative and will not receive a referral.

After dental examinations, screened-positive children in the intervention group will be referred to a specific hospital for treatment (referral to a specific treatment facility), King Saud University Dental College (KSU-DC). Referral to this specific institution is one of the innovations in the proposed research. The triage unit at KSU-DC will provide any urgent care needed and make an appointment for subsequent care. All treatments will be provided free of charge. Screened-positive children in the comparison group will receive the currently accepted practice for school-based dental screening; that is, a letter will be sent to parents informing them of the child’s dental problem and advising to take them to a dentist (conventional screening). For both groups, referral letters will be sent to parents through children’s school bags.

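### Both arms are screened, so the trial compares facility referral with a letter; the secondary aim and the pre-stated conclusions about screening itself go further than the design allows

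*Protocol article*

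**What the plan says.** On the design, Trial interventions is explicit. "Children in both groups will be examined for dental caries", and "The difference between the two trial groups lies in the referral mechanism". Screened-positive children in the intervention group go to the dental college, where a triage unit gives urgent care and books further appointments, all free of charge. For the other group, "Screened-positive children in the comparison group will receive the currently accepted practice for school-based dental screening", meaning a letter advising parents to see a dentist. There is no unscreened arm: "A comparison against no intervention was disregarded due to ethical concerns".

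Four places then speak about screening itself.

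- Abstract, Discussion: "This project should provide high level of evidence on the clinical benefits of school dental screening".
- Background, aims: "A secondary aim is to determine the effectiveness of school-based dental screening among population subgroups". Supplemental analysis restates this as the purpose of the subgroup analysis.
- Discussion, positive result: "If the research shows a positive impact it will set the scene for recommending the implementation of school-based dental screening nationally". The next sentence treats a positive finding as a reason to keep whatever screening programmes already run elsewhere in the country.
- Discussion, null on both outcomes: "lack of effectiveness in both uptake of services and clinical outcome will reflect problems with the overall screening process".

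**The concern.** The conclusions need a comparison that the trial does not contain. Advising that schools should screen needs an estimate of screening against no screening. The trial estimates one referral pathway against another in children who have all been screened.

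Both directions of result are affected. A positive result shows that facility referral does better than the letter, which is not the same as showing that screening does better than none. A null result on visits and caries would be put down to the screening process, although two routes that work equally well give the same data. The abstract says the findings should inform whether school screening is continued or introduced in Saudi Arabia, so a policy reader could act on a question that was not tested.

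**Working it through.** The plan gives no figure on this point, so the check sets the randomised contrast beside the stated conclusions.

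**What the trial estimates.** Let the mean 12-month change in number of untreated decayed teeth be:

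- Y0 with no school screening (not observed in this trial);
- YL with screening plus a letter (comparison arm);
- YF with screening plus facility referral (intervention arm).

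The trial estimates D = YF − YL. The effects of screening against none are SL = YL − Y0 for the letter version and SF = YF − Y0 for the facility version. Hence D = SF − SL, and Y0 drops out. The sample-size section powers the same D: a 0.50-tooth difference between the conventional and the specific screening groups.

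**Null result.** The values of SL and SF below are illustrations, not figures from the protocol; negative means fewer decayed teeth.

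| SL | SF | D = SF − SL |
|---|---|---|
| 0 | 0 | 0 − 0 = 0 |
| −1 | −1 | −1 − (−1) = 0 |

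Screening does nothing in the first row and removes one untreated decayed tooth per child in the second, and the trial cannot tell them apart. The second row is not far-fetched here: the Background says free dental care is available through the health ministry, university hospitals and military health services, so families who receive only the letter also have free options.

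**Positive result.** Take D = −0.50, the size the trial is powered for.

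| SL | SF | D = SF − SL |
|---|---|---|
| 0 | −0.50 | −0.50 − 0 = −0.50 |
| −1 | −1.50 | −1.50 − (−1) = −0.50 |
| +0.50 | 0 | 0 − 0.50 = −0.50 |

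If one assumes SL ≤ 0 (screening plus a letter is no worse than no screening), then SF = D + SL ≤ −0.50, and the facility package beats no screening. Without that assumption the third row remains possible. The protocol does not test the assumption, and its Background reports that systematic reviews left both harm and benefit of school screening uncertain. Even with the assumption, nothing follows about the size of SL, the effect of letter-based programmes.

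**Existing programmes.** Trial interventions defines the comparator as currently accepted screening practice. A positive superiority result means that this practice did worse than facility referral. The Discussion nevertheless offers a positive result as grounds for continuing existing programmes without distinction, which would include letter-based ones.

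**Secondary aim.** Supplemental analysis meets it by comparing the two trial groups among screened-positive children and then among regular attenders. Each is D within a subgroup. The analysis is sound for the referral contrast and does not deliver the aim as worded.

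**Within-arm change.** YL and YF are each measured against baseline, not against Y0. Children are a year older at follow-up, and caries counts change with age and with the loss of primary teeth, so a before-after change cannot stand in for a screening effect.

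**The case against.** The strongest reply is that the operative parts of the protocol are right. The primary aim compares two approaches to screening, the sample size and the effect estimates use that contrast, and the absence of an unscreened arm is disclosed with a reason. This stands: no outcome, model or procedure is at fault. A reader might infer that the design or the primary aim is defective, but the documents do not support that.

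It can also be said that the secondary aim is shorthand, since Supplemental analysis goes on to describe a between-group comparison. Nobody would run the wrong analysis from it. But the aim is formally stated, and its wording matches the overreach in the abstract and the Discussion, so it should be aligned.

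Three stronger readings should be resisted.

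- *The trial says nothing about screening in either direction.* This is too absolute. A positive result is informative about the facility package under the assumption shown above.
- *The plan treats any null as failure of screening.* It does not. The sentence on the screening process applies when both uptake and clinical outcome show no effect. Elsewhere the Discussion says a lack of benefit would only highlight the need to examine existing programmes. The objection is to that one sentence. Even if its process is taken to include referral, equal arms do not show a problem.
- *Only the destination of the referral differs.* The facility arm also brings triage, appointments and free treatment there.

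The Discussion's language is partly tentative, and it concedes that not all questions about screening will be answered. That caveat concerns limited resources, cost-effectiveness and geographic reach. It does not say that screening versus none cannot be estimated.

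**Conclusion.** The concern holds as a mismatch between the design and the stated conclusions. The trial can estimate facility referral versus letter among screened schoolchildren. It does not estimate screening versus no screening, and the abstract, the secondary aim with its restatement, and the Discussion are worded as if it did.

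The size is logical rather than numerical. A null is compatible with any screening effect common to both arms. A positive result bears on screening only for the facility package, and only if screening plus a letter is no worse than none; it gives no support to letter-based programmes. This conclusion rests on the protocol's own account of the two arms and on no outside figure. The change is worth making because it alters what may be concluded, while the primary analysis stays as it is.

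**What to change.** Reword the conclusions in the abstract and the Discussion, and align the secondary aim in the Background and the opening of Supplemental analysis, so that all refer to the effect of referral to a specific facility versus a letter among screened schoolchildren. Then:

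- Positive result: supports adding facility referral where screening is already done. Drop the inference to national screening and to continuing existing programmes in general.
- Null result: no evidence that facility referral improves on the letter, reported with its confidence interval. Drop the attribution to the overall screening process.
- State once, plainly, that the effect of screening versus none is not estimated.
- State that change from baseline within an arm will not be read as a screening effect.

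The cost is wording and a narrower claim. Design, sample size, data collection and planned models are unchanged.

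### Both groups are screened, so a null result would not show that screening has failed, and a positive result would not justify continuing existing letter-based programmes

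*Protocol article*

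**What the plan says.** The Trial interventions section of the protocol article fixes the comparison. "Children in both groups will be examined for dental caries", and "The difference between the two trial groups lies in the referral mechanism". Screened-positive children in one group are referred to a named dental college. Those in the other group receive a letter advising a dental visit, which the section calls "the currently accepted practice for school-based dental screening". There is no unscreened arm, and the reason is given: "A comparison against no intervention was disregarded due to ethical concerns".

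The Discussion then says in advance how the result will be read:

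- If there is no effect on either outcome: "lack of effectiveness in both uptake of services and clinical outcome will reflect problems with the overall screening process".
- If the result is positive: "If the research shows a positive impact it will set the scene for recommending the implementation of school-based dental screening nationally".
- Also if the result is positive: "A positive finding will also provide the grounds for continuation of any existing screening programme in other parts of the country".

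Similar wording appears in the Background: "A secondary aim is to determine the effectiveness of school-based dental screening among population subgroups". The primary aim in the same paragraph, however, is framed correctly as a comparison of two approaches to screening and referral.

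**The concern.** The trial randomises the referral route, but the Discussion draws conclusions about screening as such. With both groups screened, whatever effect the two forms of screening share cancels out of the between-group difference.

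The Abstract and the Discussion both direct the findings at policy on continuing or introducing school screening. If the stated readings were carried into the report, a null could be used against a letter programme that works. A positive result could be used to keep a letter programme that does not.

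**Working it through.** No figure in the plan is in dispute. The check is what the randomised contrast can and cannot identify.

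**Inputs**
- Both groups screened, referral route differs, no unscreened arm: Trial interventions.
- Target difference of 0.50 teeth with untreated caries between the groups: Justification of sample size. It is used here only as a convenient scale.
- Effect of letter screening against no screening: not given. Assumed range 0 to 0.50 teeth prevented per child, plus one harmful value (−0.50), because the Background reports that systematic reviews were uncertain of either harm or benefit.

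**Notation.** Let L and F be the untreated decayed teeth prevented per child over 12 months by letter screening and by facility-referral screening, each against no screening. The trial estimates D = F − L, so F = L + D.

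| Assumed L | F if D = 0 (null) | F if D = 0.50 (plan's target) |
|---|---|---|
| −0.50 | −0.50 | 0 |
| 0 | 0 | 0.50 |
| 0.25 | 0.25 | 0.75 |
| 0.50 | 0.50 | 1.00 |

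**Null result.** D = 0 holds in the row where screening does nothing (0, 0) and in the row where both forms prevent half a tooth per child (0.50, 0.50). The same subtraction applies to dental visits, so adding a null on uptake does not separate these cases. Reading the null as a fault in the screening process requires L to be zero or negative, and the article gives no basis for that.

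**Positive result, existing programmes.** L takes the same values in the D = 0.50 column as in the D = 0 column, so the result carries no information on L. For a programme that uses the letter, what has been shown is that its referral route is inferior. Whether it is better than nothing depends on L. The article does not describe how existing programmes refer, so a statement covering all of them has no support.

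**Positive result, national implementation.** If L is at least 0, then F = L + 0.50 is at least 0.50 in every row, so facility-referral screening beats no screening. If L = −0.50, then F = −0.50 + 0.50 = 0 and there is no gain over no screening. The implementation sentence is therefore defensible for the facility-referral form of screening, under an assumption the article does not state.

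**Consistency of the two readings.** Reading a null as failure of screening needs L ≤ 0. Reading a positive result as grounds to continue a letter-based programme needs L > 0. No single assumption about L supports both.

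**The case against.** The strongest reply is that the article treats screening as more than the examination. The Background argues that a screening programme needs a support system to get children to treatment, and the Discussion presents facility referral as the step that earlier studies lacked. On that view, the phrase about the screening process means the enhanced package, and the null sentence says only that the package added nothing. This is a fair reading of loose wording, but it does not rescue the inference. A package that adds nothing to the letter may still be working as well as the letter does.

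Second, the article contains caution. The Discussion says that a finding of no benefit would call for proper evaluation of existing programmes, and it concedes that not all questions about school screening will be answered. Trial interventions openly discloses the missing no-intervention arm. These points lower the severity. But the concession is tied to limited PhD resources, and neither hedge says that screening against no screening is not estimated.

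Third, dental visits are asked about at both waves in both groups (Data collection), so a rise common to both would be visible. It would, however, be a before-after change without an unscreened control.

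Three stronger readings might be inferred and are not supported:

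- *A positive result says nothing about screening.* This goes too far: if letter screening does no harm, a true advantage for facility referral means that facility-referral screening beats no screening.
- *The secondary aim and the subgroup analyses target the wrong quantity.* The label is loose, but Supplemental analysis states that outcomes are compared between the two trial groups.
- *The trial needed an unscreened arm.* The article gives an ethical reason for not having one, and the primary aim, sample size and between-group analysis all address the comparison actually randomised.

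**Conclusion.** The point holds for two sentences of the Discussion: the one on a null in both outcomes, and the one on continuing existing programmes. Neither follows from a comparison of facility referral with a letter among screened children. The national-implementation sentence needs a qualification, not removal.

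Severity is minor. The point concerns what may be concluded, not how the trial is run, sized or analysed. The tabulated values rest on an assumed range for L; they demonstrate non-identification and do not estimate any impact. The conclusions about the null and about existing programmes do not depend on that range. The partial defence of the implementation sentence does depend on letter screening being no worse than no screening.

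**What to change.** Reword three sentences in the Discussion.

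1. Replace the sentence on a null in both outcomes with:

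> If no difference is found in uptake or caries, the trial will not have shown that referral to a specific treatment facility improves on conventional referral, within the limits of the confidence interval; it will not show whether screening itself works.

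2. Replace the sentence on continuing existing programmes with:

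> A positive finding would support using referral to a specific treatment facility rather than a conventional letter where school screening is carried out.

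3. Keep the national-implementation sentence, but limit it to screening with facility referral. Add that it assumes conventional letter screening is no worse than no screening, because screening against no screening is not estimated.

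Relabelling the Abstract's discussion paragraph, the secondary aim and Supplemental analysis so that they name the referral comparison is optional.

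The cost is wording only, with no change to design, sample size or analysis. The downside is a narrower policy claim.
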